#### HUS internet delivered therapist assisted therapy for persistent somatic symptoms

The HUS internet delivered therapist assisted therapy for persistent somatic symptoms is based on acceptance and commitments therapy (ACT) and includes psychoeducation as well as exercises aimed at improving wellbeing by relaxing the body and learning new ways of observing the symptoms, and psychological flexibility by developing acceptance and self-compassion. The program consists of ten modules at 1-week intervals lasting 10 weeks altogether. The participant receives weekly written feedback on each module by a trained therapist (psychologist, nurse or social worker). The provider of the program monitors the steps finished and the progress made by the patient. The patient needs to have an e-mail address, an electronic device (smartphone, tablet or computer) and means for electronic identification in order to receive the intervention. As an intervention this e-therapy is available for patients both in primary and secondary care. For this trial we enroll only patients who have not received the intervention previously.

In addition to the study intervention, patients receive treatment as usual (TAU).

#### Treatment as usual (TAU)

The patients have an initial appointment with a physician and may in addition have appointments with a physiotherapist, an occupational therapist, a psychologist and/or a social worker. If needed, the patient can be in contact with the physician remotely (by phone or message in a patient portal) or at a control appointment. Patients may also attend group interventions. If possible, medication is kept the same during the intervention and three months afterwards. If there is need to change the medication during the trial, the changes will be recorded. We will also record the use of other simultaneous interventions (such as e.g. psychotherapy). Appointments with health professionals and attendance in group interventions are documented in the electronic patient record system.

The control group consists of treatment as usual for six months, which is the primary end point of the study. After this, control patients are offered the possibility to take part in either the AIR program or the HUS internet therapy if they so wish.

### Outcome assessment

The primary outcomes in the study are self-reported functional ability and quality of life as measured on a scale from 0 to 10 and functional ability measured by the WHO Disability Assessment Schedule (WHODAS) instrument at six months. All outcomes of the study are presented in Table 1.

**Table 1 pone.0316169.t001:** Outcomes of the RCT and the timepoints of measurement.

	Baseline, 0 months	3 months	6 months	12 months
**Primary outcome measures**				
Functional ability 0–10	x	x	**x**	x
Quality of life 0–10	x	x	**x**	x
Functional ability: WHODAS2.0	x	x	**x**	x
**Secondary outcome measures**				
Baseline information: other chronic diseases, medications, social status, occupation	x			
Follow-up questionnaire (PREMs, treatments, feedback)		x	x	x
Quality of life: EuroHIS-QOL-8, [50]	x	x	x	x
Health related Quality of life: 15D [51]	x	x	x	x
Symptoms, SSD-12 [52] and PHQ-15 [53]	x	x	x	x
Depression, PHQ-9 [53]	x	x	x	x
Anxiety, GAD-7 [54]	x	x	x	x
ISI, Insomnia Severity Index [55]	x	x	x	x
Work ability (subjective, three steps) [56]	x	x	x	x
Resilience	x	x	x	x
Resilience Scale-14 (RS-14) [57]				
Researcher collects information from patient health record: diagnoses, medications, healthcare use, and other possible treatments during 12 months				x

In addition to the collected patient reported outcome measures (PROM), at 3, 6 and 12 months, we will collect information on patient reported experience (PREM) of the treatment received and of participating in the AIR trial.

We will perform a modifier analysis on baseline characteristics that may influence outcome impact.

### Statistical analysis

A research assistant will store the baseline data in pseudonymized format into the HUSeCRF database. Access to the database is given to those members of the research group who analyze the data. Access to HUSeCRF is with personal codes and includes phone verification.

The codes that link patient information and study numbers are saved in the Key register, which can only be accessed by the PI and the study coordinators.

### Analysis plan

All randomized participants will be analyzed in accordance with the intention-to-treat principles. Baseline data will be summarized as counts and percentages for categorical variables and mean values with standard deviation (SD) or median values with interquartile ranges (IQRs) for normally distributed or skewed continuous variables, respectively. Changes in primary and secondary outcomes over time and differences between intervention groups will be examined using generalized linear mixed models with time (0, 3, 6 and 12 months), intervention group, and interaction between group and time as fixed effects, and participants as a random effect. The most suitable correlation structure will be determined from the data based on multiple measures, including Akaike’s and Bayesian Information Criteria. Causal Directed Acyclic Graphs will be used in order to select a minimal adjustment set of fixed effect variables for mixed modeling on repeated measures. Benjamini–Hochberg procedure will be applied to correct for multiple testing. The statistical analyses will be carried out using R statistical computing environment [58].

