**Methods:**

We will perform a randomized controlled trial aiming at 360 patients. Consenting patients will be randomized to three study arms: online AIR program, HUS iCBTpss (both interventions as add-ons to TAU); and TAU. Functional ability and quality of life surveys will be collected from participants at baseline and at 3, 6, and 12 months after entering the study.

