### Study flow

In the beginning, the patient receives written information and an oral explanation of the study from the physician and is asked to give written informed consent. Patients have the right to withdraw from the study at any point if they so wish with no consequences to their treatment.

The patients are asked to give their consent to participate in the study via the Suomi.fi-service, an electronic service requiring strong identification. The research assistant signs the consenting patients in the Helsinki University Hospital Electronic Case Report Form (HUSeCRF) system which randomizes the patients. The patients then fill in the baseline information forms online in the HUSeCRF system. The research assistant has access to the interim results. In case the research assistant reports significant differences in outcomes between intervention and control groups midway through the study, the study will be terminated earlier than planned.

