### Participants and recruitment

#### Inclusion criteria

Age 18 to 65 yearsPersistent somatic symptoms, fibromyalgia, chronic fatigue syndrome, and post COVID-19 as predefined subgroups (please see S1 Appendix. Diagnostic criteria).

Diagnostic examinations have ruled out the potential somatic or psychiatric reasons for the symptoms ANDDisabling symptoms have lasted at least 3 months ANDPatient is willing to receive an online, mostly self-management intervention.

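### The covariate rule is a confounding criterion that cannot select prognostic covariates in a randomised comparison, and month 0 is modelled with unconstrained arm means, so the 6-month contrast loses precision

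*Protocol article*

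**What the plan says.** Allocation is random: "Consenting patients will be randomized to three study arms" (Abstract, Methods). The primary time point is six months; the Treatment as usual section describes the control condition as "treatment as usual for six months, which is the primary end point of the study".

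The Analysis plan specifies a mixed-model analysis of the repeated measurements. Its terms are these: "time (0, 3, 6 and 12 months), intervention group, and interaction between group and time as fixed effects, and participants as a random effect". Month 0 is thus an outcome level, and each arm has its own baseline mean. Further covariates come from a single rule: "Causal Directed Acyclic Graphs will be used in order to select a minimal adjustment set of fixed effect variables". The article neither names a covariate nor says what the graph would contain.

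Information that could improve precision is available. Table 1 has all three primary outcomes measured at month 0, together with "Baseline information: other chronic diseases, medications, social status, occupation". The Inclusion criteria list fibromyalgia, "chronic fatigue syndrome, and post COVID-19 as predefined subgroups". The Introduction names two recruiting clinics.

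On timing, the Study flow section says that the electronic system randomises the patient, and continues: "The patients then fill in the baseline information forms online in the HUSeCRF system".

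**The concern.** There are two reasons to adjust in an analysis: to remove confounding, or to reduce residual variance. In a randomised comparison the first does not arise for the total effect, and the second is the reason to adjust. The stated rule serves the first purpose only. A variable that predicts the outcome but not the allocation lies on no confounding path, so a minimal set leaves it out. Adding diagnosis group or clinic for precision would depart from the rule as written.

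The model also lets the arms differ freely at baseline, although randomisation makes their expected baseline means equal. That information goes unused. At stake are wider intervals than necessary for both comparisons with usual care and for the comparison of the two online programmes.

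**Working it through.** **The plan's own figures.** The Power calculations section gives at least 90 per group for power above 80%, raised to 120 per arm; the Design section gives 360 in total. The totals agree: 3 × 120 = 360, and 90 / (1 − 0.25) = 120, an implied loss of 25%. The 90 itself cannot be reproduced from the article, which gives no effect size, SD, significance level or correlation and refers to S2 Appendix. Assuming two-sided 0.05, 90 per group has 80% power for a simple two-group difference of (1.960 + 0.842) × √(2/90) = 0.418 SD.

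**The covariate rule.** In a causal graph, a randomised arm has no cause other than the randomiser. No back-door path runs from arm to outcome, so the minimal set for the total effect is empty. This is an inference from the method; the article does not state it.

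**The role of baseline.** Let r be the correlation between baseline and month 6 (assumed; the article gives none), with equal variances. In units of 2σ²/n, the variance of a two-arm contrast at 6 months is:

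- change from baseline (the group-by-time contrast): 2(1 − r)
- group difference at 6 months, arm means unconstrained: 1
- common baseline mean, or baseline score as covariate: 1 − r²

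The saving from adjustment is therefore 1 − (1 − r²)/[2(1 − r)] = (1 − r)/2 against change, and r² against the 6-month difference.

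| r | Change | Difference | Adjusted | Saving vs change | Saving vs difference |
|---|---|---|---|---|---|
| 0.3 | 1.40 | 1.00 | 0.91 | 35% | 9% |
| 0.5 | 1.00 | 1.00 | 0.75 | 25% | 25% |
| 0.7 | 0.60 | 1.00 | 0.51 | 15% | 49% |
| 0.8 | 0.40 | 1.00 | 0.36 | 10% | 64% |

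A generalized least squares calculation for three arms and months 0, 3, 6 and 12 reproduced these values under both exchangeable and decaying correlation.

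**Power, complete data, 90 per arm, difference 0.418 SD.** At r = 0.5, either unconstrained contrast has 80.0% and the adjusted one 89.9%. At r = 0.7, the change contrast has 95.1%, the 6-month difference 80.0% and the adjusted contrast 97.5%.

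**With loss to follow-up.** The calculation was repeated with 120 per arm and 25% monotone loss by month 6 (half before month 3, half between months 3 and 6). The variance ratio of change to adjusted becomes 1.41–1.42 at r = 0.3, 1.25–1.26 at 0.5, 1.14 at 0.7 and 1.09 at 0.8. Taking 1 − 1/ratio, the savings are about 29%, 20–21%, 12% and 8%. Against the 6-month difference the ratios are about 1.08, 1.25–1.26, 1.74–1.77 and 2.37–2.42, or savings of about 7%, 20–21%, 42–43% and 58–59%.

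These figures concern the baseline score alone. The further gain from diagnosis group, clinic, age and sex cannot be sized, because the article does not say how strongly they predict the outcomes.

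**The case against.** The strongest reply is that this is a condensed article. Covariate lists and the exact 6-month contrast are commonly left to the analysis plan, and the unconstrained longitudinal model is standard and unbiased. That stands as far as it goes: the absence of a covariate list is not the point. The point is the rule that the article does state, which serves the wrong purpose for a randomised comparison, and the baseline structure that it does specify.

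A graph that includes dropout could return a non-empty set. That is true, but the article gives no such purpose, and such a set would still not be chosen for precision.

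A reader might infer several stronger points that the documents do not support:

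- *The rule leads to adjustment for variables arising after randomisation.* The usual-care section says "If there is need to change the medication during the trial, the changes will be recorded", but nothing proposes adjusting for those changes. A correctly drawn graph for the total effect would exclude them.
- *Baseline information is thrown away.* Under the change contrast it is used, only not fully, and the loss shrinks as r rises.
- *The trial gives up the equivalent of 120 rather than 90 evaluable patients per arm.* That ratio, 1/0.75 = 1.33, needs r = 0.5 and complete data. With 25% loss it is about 1.25.
- *The trial is underpowered as a result.* The simulations are in an appendix not shown and may already reflect repeated measures.
- *Diagnosis and clinic are strong predictors.* This is plausible, but nothing in the article shows it.

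A final objection concerns the remedy. Baseline forms follow randomisation, and the arms are easily told apart. If patients knew their arm when they answered, adjusting for the baseline score or constraining its mean could introduce bias. This stands, and the remedy must be conditional on it. It does not defend a change contrast, which relies on the same baseline answers.

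**Conclusion.** The point holds as a matter of efficiency. The covariate rule offers no way to select prognostic variables for the randomised comparisons, and the unconstrained baseline costs precision under either reading of the 6-month contrast for any r strictly between 0 and 1. The treatment estimate is not biased by leaving covariates out.

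The size depends on r, on which contrast is primary and on the extent of loss, so the tabulated ranges are illustrations under stated assumptions and not properties of this trial. How much can safely be recovered through the baseline score depends on whether allocation was known when the baseline forms were completed, which the article leaves open. The change is worth making, but its absence would not invalidate the trial.

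**What to change.** 1. For the randomised comparisons, replace the DAG step with a short prespecified list of covariates that allocation cannot affect: diagnosis group as established at inclusion, clinic, age and sex. These are safe whatever the order of baseline forms and randomisation. Keep DAGs for non-randomised questions.
2. Establish whether patients completed the baseline forms before they knew their arm.
3. If they did, fit the longitudinal model with a common baseline mean across arms, or use the baseline score as a covariate with the post-baseline visits as outcomes. Under a common baseline mean, the change contrast and the 6-month difference coincide, which also settles which of the two is meant.
4. If they knew their arm, report the baseline-adjusted result only as a sensitivity analysis.

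The cost is revised wording, a little more analysis work and a check of the order of baseline and allocation. The sponsor should also confirm that sex and clinic are held in the database, since the baseline row of Table 1 does not list them. The trial was ongoing at publication, so baselines already collected cannot be reordered; the second step must rest on what was actually done.

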### Power calculations

It is hypothesized that the AIR program is equal in effect to the e-therapy. Additionally, it is hypothesized that both the AIR program and the e-therapy are more effective than TAU. According to simulations carried out based on a previous report [25] it was estimated that a sample size of at least 90 individuals per experimental group is required for reaching statistical power of >80% for outcome measures demonstrating improvement in AIR patients as compared to treatment equivalent to relaxation therapy (RT). This sample size was sufficient for all 9 out of 9 previously studied outcome measures reflecting functional impact, clinical severity, pain catastrophizing, severity of anxiety and depressive symptoms, perceived health status, psychological inflexibility, and mindfulness at post-treatment and three-month follow up. To overcome loss to follow up, we aim at 120 patients per each treatment arm. Please see details on the power analyses in S2 Appendix.

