Many treatment options are based on cognitive behavioral therapy (CBT). A review of randomized controlled trials assessing the efficacy of treatment for somatoform disorders indicated that CBT is the best-established treatment for a variety of these disorders [17]. Later, a Cochrane review assessed psychological therapies, especially CBT, in medically unexplained symptoms [18]. They were superior to treatment as usual or waiting list in terms of reduction of symptom severity, but effect sizes were small. Similarly, another Cochrane review found that CBT is effective in reducing the symptoms of chronic fatigue syndrome (ME/CFS) compared with usual care and may be more effective in reducing fatigue symptoms compared with other psychological therapies [19].

However, CBT is not widely available and patients suffering from persistent somatic symptoms are many. There is some evidence that CBT administered as internet therapy is effective in ME/CFS [20]. Acceptance and commitment therapy (ACT) is a form of cognitive behavioral therapy which uses acceptance and mindfulness strategies together with commitment and behavior-change strategies to strengthen behavior consistent with personal values as well as to increase psychological flexibility [21]. There is evidence that ACT in a Web-based delivery format was effective in the management of depression [22]. A web-based ACT-program has been developed by the University of Jyväskylä with expertise from the Finnish Institute of Occupational Health and is provided by the Hospital District of Helsinki and Uusimaa, which has already provided web-based treatments for various other conditions.

Easily available non-drug-based therapies are needed for the treatment of patients with persistent somatic symptoms. There is some evidence that neuroplasticity techniques may be effective in the treatment of ME/CFS [23, 24] and fibromyalgia [25] as well as post COVID-19 condition [26]. The amygdala and insula retraining program is developed by [name] and is based on the hypothesis, that in the presence of dysregulating factors (e.g. physiological stressors), the amygdala can become chronically sensitized to bodily signals by a traumatic event (e.g. viral infection) leading to a chronic over-activation of the sympathetic nervous system [24].

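### The stated >80% power is for AIR against relaxation therapy on an earlier report's measures, not for this trial's hypotheses on its six-month primary outcomes

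*Protocol article*

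**What the plan says.** The Power calculations section of the protocol article opens with the trial's hypotheses: "It is hypothesized that the AIR program is equal in effect to the e-therapy", and "both the AIR program and the e-therapy are more effective than TAU". It then says that, from simulations based on one previous report, "a sample size of at least 90 individuals per experimental group is required" to reach "statistical power of >80% for outcome measures demonstrating improvement in AIR patients as compared to treatment equivalent to relaxation therapy (RT"). The size is said to suffice for all nine measures in that report, a list that ends with "perceived health status, psychological inflexibility, and mindfulness at post-treatment and three-month follow up". The target becomes 120 per arm to allow for loss to follow-up, and further detail is left to S2 Appendix, which is not shown.

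Elsewhere the article defines a different set of comparisons. The abstract states: "Consenting patients will be randomized to three study arms: online AIR program, HUS iCBTpss (both interventions as add-ons to TAU); and TAU". Outcome assessment names three primary outcomes: functional ability on a 0–10 scale, quality of life on a 0–10 scale, and "functional ability measured by the WHO Disability Assessment Schedule (WHODAS) instrument at six months". The Analysis plan applies a Benjamini–Hochberg correction for multiple testing.

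**The concern.** The paragraph moves from the trial's own hypotheses to a power figure for another contrast without connecting the two. A reader will take >80% as the power of this trial. A non-significant iCBT–TAU result, or a non-significant AIR–iCBT difference, could then be reported as adequately powered evidence of no benefit or of equality, although the article's figure addresses neither.

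The article's background gives a reason for caution about the size of effect against TAU. Of psychological therapies for medically unexplained symptoms it says: "They were superior to treatment as usual or waiting list in terms of reduction of symptom severity, but effect sizes were small". It gives no number, and the statement concerns symptom severity rather than this trial's primary scales. It therefore supports showing a range that includes smaller effects, not adopting a particular value.

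**Working it through.** **1. What was powered, beside what will be tested**

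| Element | Power calculations | This trial |
|---|---|---|
| Contrast | AIR vs relaxation therapy | AIR vs TAU; iCBT vs TAU; AIR equal to iCBT |
| Outcomes | nine measures of the earlier report | functional ability 0–10, quality of life 0–10, WHODAS |
| Time | post-treatment and three months | six months |

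iCBT appears in both hypotheses but not in the calculation as the article states it.

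**2. The plan's own figure**

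The 90 per group cannot be reproduced, because the article gives no effect size, SD, alpha or sidedness. Those may be in S2 Appendix, so their absence is not a criticism. The figure can be solved backwards with the normal approximation for two means:

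d = (z for alpha + z for power) × √(2/n)

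- Two-sided 5%, 80% power, n = 90: (1.960 + 0.842) × √(2/90) = 0.418.
- One-sided 5%: (1.645 + 0.842) × √(2/90) = 0.371.

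The allowance for loss is consistent: 90/120 = 0.75, so 120 per arm with 25% loss leaves 90.

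**3. Power for one TAU contrast on one outcome**

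Inputs: 90 evaluable per arm from the article; two-sided 5% assumed; effect sizes d assumed. Power = Φ(d × √(90/2) − 1.960), with √45 = 6.708.

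| d (assumed) | d × 6.708 | Power |
|---|---|---|
| 0.20 | 1.342 | 27% |
| 0.30 | 2.012 | 52% |
| 0.42 | 2.817 | 80% |
| 0.50 | 3.354 | 92% |

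**4. Effect of the planned Benjamini–Hochberg correction**

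This was simulated with 90 per arm, d = 0.418 in both TAU contrasts, a shared TAU arm, and correlation between the three outcomes assumed at 0 to 0.7.

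- Six tests (3 outcomes × 2 TAU contrasts): average power per test about 75–77%.
- Nine tests, adding three AIR–iCBT tests with no true difference: about 69–71% for the six TAU tests.

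**5. Both interventions significant against TAU on one outcome**

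The two test statistics share the TAU arm, so their correlation is 0.5. With each contrast at 80% power (d = 0.418), the bivariate normal probability that both are significant is 69%.

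**6. The equality hypothesis**

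The article gives no margin. With two one-sided 5% tests and a true difference of zero, power = 2Φ(margin × √45 − 1.645) − 1. The margin that gives 80% power is (1.645 + 1.282) × √(2/90) = 0.44 SD. At a margin of 0.3 SD power is 29%, and at 0.4 SD it is 70%.

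**The case against.** The strongest defence is that the relaxation-therapy simulation was a reasonable stand-in and that the working is in S2 Appendix. Relaxation therapy may have been meant to represent TAU. Functional impact in the earlier report is close in concept to functional ability. Anxiety and depression are secondary outcomes here, and three months is a scheduled visit. All of that stands, and it is why the point is limited to the stated hypotheses on the primary outcomes at six months. It does not rescue the figure. The appendix may supply inputs or a rationale, but it cannot change the contrast, measures and time points that the article itself attaches to the >80%. The article does not say that relaxation therapy represents TAU, and if it does, iCBT versus TAU and the equality hypothesis remain uncovered.

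Four stronger readings are tempting, and the documents do not support them.

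- **That 120 per arm is too small.** The effect sizes above are assumptions. At 0.50, 90 evaluable per arm give 92%. The value 0.42 is solved from exactly 80%, whereas the article claims more than 80% on all nine measures, so the simulated effects may be larger.
- **That the trial succeeds only if both interventions beat TAU.** The article states this as a hypothesis and nowhere makes joint significance the criterion.
- **That multiplicity removes most of the power.** A Bonferroni calculation would suggest a large loss, but the plan names Benjamini–Hochberg, and the loss is about 3 to 11 percentage points from 80%.
- **That the AIR–iCBT comparison is underpowered for equivalence.** Without a margin, its power can be neither asserted nor denied.

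**Conclusion.** The point holds in this form: the >80% and the 90 per group describe AIR against relaxation therapy on another study's measures at post-treatment and three months. They are not the power for AIR versus TAU, iCBT versus TAU, or AIR equal to iCBT on the three primary outcomes at six months. On the most favourable reading they inform AIR versus TAU only, before the primary time point. This is a mismatch between the justification and the tests, not an arithmetic error.

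What 90 evaluable per arm offer for a single TAU contrast runs from 27% to 92% as the standardised difference goes from 0.20 to 0.50. This assumes a two-sided 5% level, one unadjusted test and no gain from baseline adjustment. The Benjamini–Hochberg figures also assume equal effects of 0.42 in both TAU contrasts on all three outcomes, and outcome correlations between 0 and 0.7.

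**What to change.** Rewrite the Power calculations paragraph and leave the sample size as it is.

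1. State power per TAU contrast on a six-month primary outcome as a range, with the assumptions visible: 90 evaluable per arm, two-sided 5%, one unadjusted test; 80% at a standardised difference of 0.42, 92% at 0.50, 52% at 0.30, 27% at 0.20.
2. Add the effect of the planned correction: at 0.42 in both TAU contrasts, average power per test of about 75–77% over six tests, or about 69–71% if three AIR–iCBT tests with no true difference are in the same family.
3. If wanted, give the 69% chance that both interventions beat TAU on one outcome at 0.42, as information and not as a success rule.
4. Describe the relaxation-therapy simulation as supporting evidence for AIR only.
5. Say that the >80% does not apply to the AIR–iCBT equality hypothesis, for which the article gives no margin. With one-sided 5% tests and a true difference of zero, 90 per arm reach 80% power only for a margin of about 0.44 SD or wider.

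The cost is one rewritten paragraph and a less favourable power statement. No extra patients are needed.
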